##### Module 2: empowerment training for patient and informal caregiver

This module begins after discharge to the home environment where the treatment focus will switch to learning to cope with residual impairments as a result of a stroke. Both patients and informal caregivers will be trained by the transmural stroke coordinator in improving their coping strategies and empowerment techniques based on self-management [27,31]. The care in this module will only be given by the professionals of the multidisciplinary team of the nursing home, who are involved in the treatment based on the individual needs of the patient. The transmural stroke coordinator coordinates care in collaboration with the general practitioner.

##### Module 3: stroke education for patient and informal caregiver

The last module is a stroke education course organised for patients and their informal caregivers. This course consists of four meetings with the focus on respectively the psychological and emotional consequences of stroke, perceived problems in living independently and returning to society and the new role of the healthy partner as caregiver. The module will be provided by a neuropsychologist, two volunteers of the Dutch Stroke Patient Association and Informal Caregivers Association and a social worker. The education course is organised in cooperation with the Dutch Stroke Patient Association and Informal Caregivers Association. In this part of the intervention the transmural stroke coordinator is responsible for inviting the patients and informal caregivers to the course.

##### Usual care

The usual care of elderly stroke patients after hospital discharge consists of a multidisciplinary neurorehabilitation programme in a nursing home. Most usual care programmes focus more on the needs of the patient than the informal caregiver. Usual care is provided by a multidisciplinary stroke team also containing a nursing home physician, a general practitioner, a physiotherapist, an occupational therapist, a speech therapist and a psychologist. A transmural stroke care coordinator is not involved. After discharge the follow-up care is provided separately by community services. The medical and paramedical information about the patient is distributed by letter. The main differences between the new programme and usual care are presented in Table 1.

**Table 1 T1:** Content differences between multidisciplinary rehabilitation programme and usual care

	**Multidisciplinary transmural programme**	**Usual care**
***Care content***		
Multidisciplinary stroke team	+	+
Care based on Dutch stroke guidelines	+	+
Tailored approach with Goal Attainment Scaling	+	-
Self-management	+	-
Stroke education	+	-
Home therapy during nursing home admission	+	-
Multidisciplinary outpatient rehabilitation	+	-
Home visits of transmural stroke care coordinator	+	-
***Care organisation***		
Transmural stroke care coordinator	+	-
Multidisciplinary team meetings in nursing home	+	+
Multidisciplinary team meetings after discharge	+	-
Electronic transmural patient record	+	-

### Outcome measures

#### Effect evaluation

##### Primary outcome measures for patient

An overview of all outcome measurements per time point is presented in Table 2. Primary outcome measures are daily activity measured by means of the Frenchay Activity Index (15-items activity scale) [32], functional dependence measured by means of the Katz-15 (15-items ADL and IADL scale) [33], perceived quality of life measured by means of the Stroke Specific Quality of Life scale (49-items stroke specific quality of life scale) [34] and social participation measured by means of two subscales (autonomy outdoors and social life and relationships) of the Impact on Participation and Autonomy (scale about participation in everyday life) [35].

**Table 2 T2:** Primary and secondary outcome variables of the effect evaluation per time point

**Outcome variables**	**Scale**	**No.****of items**	**T0**	**T1**	**T2**
***Primary outcome variables***** (*****patient*****)**					
Activity level after stroke	Frenchay Activity Index	15	FI	FI	FI
Level of functioning	Katz-15	15	FI	FI	FI
Quality of life (stroke specific)	Stroke Specific Quality of Life questionnaire	49	FI	FI	FI
Social participation	Impact on Participation and Autonomy (subscales autonomy outdoors and social life and relationships)	12	FI	FI	FI
***Secondary outcome variables***** (*****patient*****)**					
Perceived health	Question 1 and 2 RAND-36	2	FI	FI	FI
Mental wellbeing	RAND-36 (subscale mental wellbeing)	5	FI	FI	FI
Social functioning	Question 10 RAND-36	1	FI	FI	FI
Quality of life	Question 1 and 2 RAND-36 and a mark for quality of life	3	FI	FI	FI
Process questionnaire patient	-	24/15	-	FI	FI
Process questionnaire informal caregiver	-	21/14	-	SQ	SQ
Cost questionnaire	-	34	FI	FI	FI
***Outcome variables***** (*****informal caregiver*****)**					
Perceived care burden	Self-Rated Burden VAS and Carer QoL	10	SQ	SQ	SQ
Objective care load	Erasmus iBMG	4	SQ	SQ	SQ
Quality of life	Question 1 and 2 RAND-36 and a mark for quality of life	3	SQ	SQ	SQ
Perceived health	Question 1 and 2 RAND-36	2	SQ	SQ	SQ
***Additional outcome measures***					
Background characteristics patient	-	10/5/5	FI	FI	FI
Background characteristics informal caregiver	-	8/7/7	SQ	SQ	SQ
Cognitive functioning patient	Mini Mental State Examination	12	FI	-	-

T0 = at baseline, T1 = after 6 months, T2 = after 12 months, FI = face-to-face interview, SQ = self-report questionnaire.

##### Secondary outcome measures for patient

Secondary outcome measures are perceived health measured by question 1 and 2 of the RAND-36 (generic quality of life scale), mental wellbeing measured by subscale mental wellbeing of RAND-36, social functioning measured by question 10 of RAND-36 and quality of life measured by question 1 and 2 RAND-36 and a mark for quality of life.

##### Outcome measures related to informal caregiver

Outcome measures are the perceived care burden measured by means of the Self-Rated Burden VAS (care burden vas scale) and the Carer QoL (carer quality of life scale) [36], objective care burden measured by means of the Erasmus iBMG (4-items care burden scale) [37], quality of life and the perceived health both measured by question 1 and 2 of RAND-36 (including a mark for quality of life) [38].

##### Additional outcome measures

Besides the primary and secondary outcomes, the following background characteristics are measured in both patients and informal caregivers: age, gender, social economic status, ethnicity, level of education, marital status, living situation, travelling distance to patient and relationship with patient. In the participants cognitive functioning is also measured at baseline by means of the Mini Mental State Examination (12-items dementia scale) [39].

##### Process evaluation

In every participating nursing home a process evaluation will be conducted in order to study factors influencing the effectiveness and feasibility of the programme and to identify potential influencing factors that can facilitate future implementation of the intervention. The process evaluation will be based on the method suggested by Saunders et al. [40] with main evaluation themes: implementation fidelity, programme delivery and the opinions of the stroke professionals, patients and informal caregivers. First, implementation fidelity will be studied by evaluating the extent to which the implementation of the programme was performed as planned. Second, programme delivery is evaluated by checking whether rehabilitation care as provided by the stroke professionals has indeed been performed according to the study protocol. Third, satisfaction of the stroke professionals, patients and informal caregivers with the programme is evaluated by assessing their opinion on various programme elements as performed.

##### Economic evaluation

The evaluation of the rehabilitation programme also involves a cost-effectiveness analysis in which we compare the programme costs and additional healthcare costs with those of usual care. The care utilisation is measured by continuously recording the volumes of health care utilisation consisting of costs for hospital admissions, structural admissions to a residential home, structural admissions to a nursing home, temporary admissions to a residential or nursing home, daytime treatment, day care, home care, mental healthcare service, social work, paramedical care and regular consultations with and visits from the general practitioner during a 12-month follow-up period.

### Data collection

Data for the effect evaluation in patients will be assembled by face-to-face interviews based on a questionnaire (including all validated measurement instruments) and in the formal caregivers by self-administered questionnaires. Trained interviewers, who are blinded for group allocation, will conduct the interviews and self-administered questionnaires at baseline, after six months and after 12 months.

Data for the process evaluation from patients, informal caregivers and health professionals are assembled by self-administered questionnaires and registration forms. To evaluate the patients’ and caregivers’ opinions about the care they received, a research assistant will conduct a semi-structured interview with all patients and informal caregivers separately to evaluate the care they received and to describe their experience of the care received in the rehabilitation programme. Furthermore, to evaluate the professionals’ opinions, a randomly selected representative sample of health care professionals will receive a questionnaire, which asks them about the programme being conducted in line with protocol, the possible reasons for deviations from protocol, the time invested, the bottlenecks identified and recommendations for improvement.

Furthermore, at the end of the intervention a focus group consisting of representatives of elderly stroke patients, informal caregivers, healthcare professionals and healthcare financiers will be organised to gather data about the implementation fidelity, programme deliverance and the opinions of the stroke professionals, patients and informal caregivers. Within the focus group semi-structured interview techniques will be used to discuss the questions about the rehabilitation programme as well as additional points raised by the participants. In order to check for contamination a selected sample of the electronic patient records will be analysed.

Data for the economic evaluation will be gathered by means of cost diaries, which are registered after six and 12 months. Healthcare costs are estimated according to the Dutch guideline for costs analyses in healthcare research [41].

### Sample size calculation

Using data from earlier research based on the Frenchay Activity Index score as primary outcome variable [42], an assumed clinically relevant difference in activity level of two stroke populations is at least 3.5 with a standard deviation of 8.9. Based on a power of 0.8 and an alpha of 0.05, the study would need a sample size of 102 patients in each group. With a drop-out to follow-up estimated at approximately 25%, each group should include 128 participants. In total 256 participants are needed for the study.

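### The 25% drop-out allowance is too small: 128 enrolled per group leaves 96, not the 102 needed for 80% power

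*Protocol article*

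**What the plan says.** The calculation stands in one paragraph of the protocol article, Methods, Sample size calculation. It is based on the Frenchay Activity Index (FAI), one of four primary patient outcomes: "an assumed clinically relevant difference in activity level of two stroke populations is at least 3.5 with a standard deviation of 8.9". The error rates follow: "Based on a power of 0.8 and an alpha of 0.05". From these the article concludes that "the study would need a sample size of 102 patients in each group". It then allows for loss: "With a drop-out to follow-up estimated at approximately 25%, each group should include 128 participants". The paragraph closes with the enrolment target: "In total 256 participants are needed for the study".

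The Data analysis section bears on this. It restricts the primary analysis to participants who have valid cost and clinical outcome data, so a patient lost to follow-up leaves the analysed number.

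**The concern.** The figure of 102 is the number that must be analysed to reach the stated power. Drop-out is a share of the patients enrolled, so the number to enrol is the analysed number divided by the proportion retained. The printed 128 looks like the analysed number increased by 25%, which is a different and smaller quantity. If so, the article's four figures (102 analysed, 25% loss, 128 enrolled, power 0.8) cannot all hold together, and the total described as needed would not deliver the power claimed for it.

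**Working it through.** **Inputs**, all from Sample size calculation: difference 3.5, SD 8.9, power 0.8, alpha 0.05, 102 per group before loss, drop-out about 25%, 128 per group enrolled, 256 in total. Sidedness is not stated.

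**1. Reproduce the 102.** For two equal groups, normal approximation, two-sided:

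n = 2 x (1.960 + 0.842)² x (8.9 / 3.5)² = 101.5, rounded up to 102.

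The t-test version gives 102.5. A one-sided test would give 80, so two-sided is the reading that matches. The plan's first figure is confirmed.

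**2. Reproduce the 128.**

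- Multiplying: 102 x 1.25 = 127.5, rounded up to 128. This matches.
- Dividing by the proportion retained: 102 / (1 - 0.25) = 136. This does not match.

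**3. What 128 leaves.**

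- At 25% loss: 128 x 0.75 = 96 per group, 192 in total, which is 6 per group below 102.
- Largest loss at which 128 still leaves 102: 1 - 102/128 = 20.3%.

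**4. Power at the number left.** With 96 per group the standard error of the difference is 8.9 x √(2/96) = 1.285, and 3.5 / 1.285 = 2.725. Power = Φ(2.725 - 1.960) = Φ(0.765) = 0.778.

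| Drop-out | Left per group from 128 | Power, normal | Power, t-test |
|---|---|---|---|
| 20% | 102.4 | 0.803 | 0.800 |
| 22% | 99.8 | 0.793 | 0.790 |
| 25% | 96.0 | 0.778 | 0.774 |
| 27% | 93.4 | 0.767 | 0.762 |

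**5. Detectable difference.** With 96 per group and 80% power: (1.960 + 0.842) x 1.285 = 3.6, against the planned 3.5.

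**6. Consistent target.** 136 per group, 272 in total, which is 8 per group and 16 overall above the printed figures. After 25% loss, 136 x 0.75 = 102 remain, with power 0.802 (normal) or 0.798 (t-test).

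**7. What baseline adjustment could recover.** Adjusting for a baseline value that has correlation r with follow-up reduces the residual variance by the factor 1 - r². For 96 patients to do the work of 102, r = √(1 - 96/102) = 0.24.

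**The case against.** The arithmetic is hard to dispute; the case on the other side is mostly about weight.

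- **The effect is small.** Power falls by 2.2 to 2.6 percentage points and the detectable difference moves from 3.5 to about 3.6. The difference is itself an assumption and the drop-out an approximation, so the inputs are uncertain by more than this. That stands as a statement of size. It does not make the printed figures consistent.
- **The drop-out rate is only approximate.** This does not help: 128 is enough only if loss stays at or below 20.3%. At 22% fewer than 100 per group remain.
- **The planned analysis may be more efficient than the sizing assumes.** Data analysis plans multiple regression, and Table 2 shows that the FAI is measured at baseline. If baseline FAI is a covariate, a modest correlation of about 0.24 would restore the loss. This is a fair limit on the consequence. However, the article names no covariates, and the sizing neither invokes adjustment nor gives a correlation, so it is a possible remedy and not a reading of the present text.
- **The multiplication is inferred.** The article prints no formula. This is true, but the finding does not depend on how 128 was reached: 128 enrolled with 25% lost does not leave 102.

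Nor can the gap be put down to a condensed article. Both the inputs and the result are printed, and the result does not follow.

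**Conclusion.** The concern holds. On the article's own assumptions, 256 enrolled leaves 96 per group, not 102, and power is about 77% to 78%, not 80%. The total consistent with 102 analysed and 25% loss is 272.

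This rests on a two-sided test (inferred, because it reproduces 102), on drop-out being a share of those enrolled, on drop-outs leaving the analysed set as Data analysis implies, and on the unadjusted two-group comparison used for the sizing. The error is objective and affects two headline design figures. It biases no estimate and does not threaten the validity of the trial.

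**What to change.** Correct the sentence on drop-out and the total that follows it. The choices are not equivalent:

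- **Restate the power (simplest).** Say that 256 randomised leaves 96 per group at 25% drop-out, with power of about 77% for a difference of 3.5. This needs no new assumption and no extra patients. The cost is one corrected sentence and a slightly less favourable power.
- **Restate the target.** Print 136 per group, 272 in total, if 80% power at 25% loss is to be kept. This costs 16 more participants. Progress of the study gives inclusion as October 2010 to September 2012, so this is open only while enrolment continues.
- **Restate the drop-out.** Say that 128 per group keeps 102 if loss is at most 20%. This changes the planning assumption, and the article offers no data for 20%, so it should be used only with a justification.

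If the sponsor wants to keep both 256 and a claim of 80% power at 25% loss, the text should name baseline FAI as a covariate in the primary analysis and state the assumed baseline to follow-up correlation. About 0.24 would suffice. The documents give no value, so it must be labelled an assumption.

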### Data analysis

The background characteristics of the participants will be described by using descriptive statistics. Baseline characteristics of the intervention and control group will be compared to detect differences at the start of the trial. Primary analyses of the effect data will be performed according to the intention-to-treat principle, including all participants with valid data on costs and clinical outcomes, regardless of whether they received the (complete) programme. Multiple regression analysis will be performed to calculate differences in the intervention and control group with regard to primary and secondary outcome measures. A per protocol subgroup analysis will be performed.

Data from the economic evaluation will be analysed to calculate cost-effectiveness and cost-utility ratios. Healthcare costs will be analysed by calculating incremental cost-effectiveness and cost-utility ratios. Data conducted from the process evaluation will be analysed by means of descriptive statistics and qualitative coding techniques. SPSS statistical software will be used for all analyses.

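### Read literally, the intention-to-treat set for the primary effect analyses requires valid cost data, so a participant with a measured clinical outcome can be left out for want of a cost record

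*Protocol article*

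**What the plan says.** In the protocol article, Data analysis, the rule opens with "Primary analyses of the effect data will be performed according to the intention-to-treat principle" and continues with the set itself: "including all participants with valid data on costs and clinical outcomes, regardless of whether they received the (complete) programme". The subject of the sentence is the effect data, and the two kinds of data are joined by a plain conjunction. The economic evaluation is treated in the next paragraph, which begins "Data from the economic evaluation will be analysed to calculate cost-effectiveness and cost-utility ratios" and gives no analysis set of its own. Nowhere does the article state a wider set for the clinical outcomes, or say that gaps in cost data are ignored or imputed for them.

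On sources, the Data collection section says of the clinical outcomes: "Data for the effect evaluation in patients will be assembled by face-to-face interviews based on a questionnaire". Of costs it says: "Data for the economic evaluation will be gathered by means of cost diaries, which are registered after six and 12 months". Table 2, however, also lists a 34-item "Cost questionnaire" among the patient measures, marked as a face-to-face interview at baseline, 6 months and 12 months, the same mode and time points as the four primary outcomes. The Economic evaluation section adds that care use is recorded continuously over 12 months.

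**The concern.** An intention-to-treat comparison keeps participants in the group to which they were randomised and loses them only where the outcome itself is missing. Here a second condition is added that does not concern the outcome. Whether a participant's cost data are valid is settled after randomisation, and it may depend on how disabled the participant is, on cognition, or on admission to an institution.

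It may also depend on arm. The Blinding section says that patients and care teams know the allocation, and Table 1 gives only the intervention arm a care coordinator who makes home visits and an electronic transmural record. If completeness of cost data is related both to arm and to outcome, dropping the incomplete participants can bias the clinical comparison in a direction that cannot be foretold.

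At stake are the validity of every primary comparison, since the rule governs all four primary outcomes, and the loss of measured outcomes for which the sample size makes no allowance: its 25% covers drop-out to follow-up only.

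**Working it through.** **Inputs.** From Sample size calculation: a Frenchay Activity Index difference that "is at least 3.5 with a standard deviation of 8.9"; "Based on a power of 0.8 and an alpha of 0.05"; 102 per group before and 128 per group after a 25% drop-out allowance. The article does not say whether alpha is one- or two-sided. The proportion of participants with a clinical score but no valid cost data is not given either; I assume 0% to 30%.

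**Step 1: the plan's own figure.** The standardised difference is d = 3.5 / 8.9 = 0.393. With two-sided alpha 0.05 and the normal approximation, n per group = 2 × (1.960 + 0.842)² / 0.393² = 101.5, rounded up to 102. This matches the article, so a two-sided test is taken below (a one-sided test would give 80).

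**Step 2: evaluable patients before any cost condition.** 128 × 0.75 = 96 per group. Two-sample t-test power with 96 per group at d = 0.393 is 0.774 (normal approximation 0.778).

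This is already below 0.80, but not because of the rule examined here. It arises because 128 is 102 × 1.25 = 127.5 rounded up, whereas 102 / 0.75 = 136 would be needed to keep 102 after a 25% loss. The cost condition should be charged only with what is lost from 0.77 downwards.

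**Step 3: add the cost condition.** Evaluable n per group = 96 × (1 − c), where c is the assumed share of participants with a valid clinical score but no valid cost data.

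| c (assumed) | n per group | Power, t-test | Power, normal approx. |
|---|---|---|---|
| 0% | 96 | 0.77 | 0.78 |
| 5% | 91 | 0.75 | 0.76 |
| 10% | 86 | 0.73 | 0.73 |
| 20% | 77 | 0.68 | 0.68 |
| 30% | 67 | 0.62 | 0.62 to 0.63 |

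(For 30%, the normal approximation gives 0.624 at 67 and 0.625 at the unrounded 67.2.)

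**Step 4: can the two kinds of data be missing separately?** Yes, but how often depends on which source the rule has in mind. If valid cost data means the diaries, a patient can be interviewed in full and still have no usable diary. If the interview questionnaire suffices, an interviewed patient would usually have cost data, apart from unanswered items among the 34. The article does not say which source counts, so neither end of the range can be ruled out.

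**Limits of the arithmetic.** The table is for an unadjusted comparison of means. The article plans multiple regression, which may have more power if the baseline score is a covariate. The table says nothing about bias, which cannot be quantified from the document.

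**The case against.** The best reply is that the phrase may be distributive: valid cost data for cost comparisons, valid clinical data for clinical ones. It is the only analysis-set statement for a study with effect, process and economic parts, the economic paragraph has none of its own, and the main purpose of the sentence seems to be to keep in participants who did not complete the programme. This reading is possible and I cannot exclude it. But the sentence speaks of effect data and does not say it, and an analyst following the text would apply both conditions. The correction is the same either way.

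A second reply is that a condensed article leaves missing-data handling to a fuller document. That would answer a complaint about silence. This is a stated rule, although a full analysis plan may define the set otherwise.

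A third reply concerns size. Table 2 places a cost questionnaire in the same interviews as the primary outcomes, and patients lost to follow-up would lack both kinds of data anyway. This stands, and it is why the range starts at zero.

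Several stronger readings are tempting but unsupported:

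- A reader might infer that clinical and cost data are unrelated streams and that a missing diary always removes the patient. Table 2 contradicts the first, and the second depends on an undefined notion of validity.
- A reader might infer that a missing 12-month diary removes a valid 6-month score. Diaries are registered at both time points and nothing in the article says so; it is conjecture.
- A reader might infer that the randomised comparison is certainly broken. Any analysis of available data conditions on observation after randomisation. What is peculiar to this rule is the subgroup with a clinical score and no cost data, whose size and relation to arm are unknown.

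**Conclusion.** The point holds as a defect in a stated rule. As written, the set for the primary effect analyses depends on cost data, carries an intention-to-treat label, and can discard measured primary outcomes for a reason irrelevant to them.

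The size is open. From 96 per group, an assumed further loss of 5% costs about 2 percentage points of power, 10% about 5 points and 30% about 16 points (0.774 to 0.618); with no further loss the cost is nil. These figures rest on the article's difference and SD, a two-sided unadjusted test, the full 25% drop-out occurring, and the cost-related loss falling on top of it. Bias is possible, but neither its presence nor its direction can be shown from the document. The fall from 0.80 to 0.77 belongs to the drop-out calculation and is a separate matter.

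**What to change.** Replace the analysis-set clause in Data analysis with:

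> The effect analysis of each clinical outcome includes all randomised participants, in the group to which they were allocated, with available data on that outcome, regardless of the availability of cost data.

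Then state any cost-data condition, or imputation of missing costs, in the economic paragraph only, and say there whether the diary, the interview questionnaire or both make cost data valid.

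This costs one rewritten sentence and a short addition to the economic paragraph. It needs no new data and no change to the planned regression. A mixed model using both follow-up times would be a reasonable option, but it is a preference and not part of this correction.

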## Background

Stroke is one of the major causes of loss of independence, decreased quality of life and mortality among elderly people [1,2]. Each year, about 45,000 people in the Netherlands suffer from stroke and associated functional impairments [3]. Almost 56% of stroke patients are 65 years or older [4].

In contrast to other countries, nursing homes in the Netherlands fulfil an important role in the rehabilitation of older stroke patients [5]. In the Netherlands, 31% of stroke patients are admitted to a geriatric rehabilitation unit in a nursing home after hospital discharge [6-8]. Stroke patients in general are admitted to a geriatric rehabilitation unit in a nursing home when they are over 65 years of age and have coexisting multimorbidity, which means that they are incapable of completing an intensive neurorehabilitation programme in a regular rehabilitation centre.

About half of the stroke patients discharged home after rehabilitation in a nursing home still experience serious impairments in daily functioning one year post stroke, that complicate fulfilling their former social roles [9-12]. Common residual problems of elderly stroke patients are emotional and psychological problems such as depression or cognitive deficits, social problems and health-related problems including rest paralysis and fatigue [13-17]. Besides having negative consequences for the patients, these problems may also increase the care burden and decrease the quality of life of their informal caregivers [18].

Currently, in the Netherlands there is a lack of tailor-made, specialised multidisciplinary aftercare following rehabilitation in nursing homes [19]. This may result in inadequate coping skills with the remaining physical, cognitive and/or psychosocial impairments in their home environment [20,21]. These problems may lead to difficulties in the performance of normal day-to-day activities, fulfilling former social roles, maintaining the functional level which has been achieved in the nursing home, and may have negative influence on the burden of care and quality of life of the patient and informal caregiver [22-24]. Eventually, permanent admission to a residential care facility or nursing home could become necessary. However, tailor-made multidisciplinary aftercare may prevent this and contribute to elderly stroke patients living independently in the community as long as possible.

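### The primary set, labelled intention-to-treat, requires valid outcome data, so as written the 12-month functional comparison is among survivors, and death is in no listed outcome

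*Protocol article*

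**What the plan says.** The Data analysis section of the protocol article says that the primary analysis of the effect data follows the intention-to-treat principle and defines the set in the same sentence: "including all participants with valid data on costs and clinical outcomes". It adds that this applies whether or not a patient had all of the programme. The model is given as "Multiple regression analysis will be performed to calculate differences in the intervention and control group", without covariates or a rule for deaths.

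On measurement, the Data collection section states: "Data for the effect evaluation in patients will be assembled by face-to-face interviews based on a questionnaire". Table 2 marks all four primary outcomes (FAI, Katz-15, stroke-specific quality of life, social participation) as interviews at every time point, with "T0 = at baseline, T1 = after 6 months, T2 = after 12 months".

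Death is not among the primary, secondary, caregiver or additional outcomes, nor among the items listed under Economic evaluation, where care use is recorded "during a 12-month follow-up period". Mortality appears only as motivation: the Abstract and the Background name "decreased quality of life and mortality among elderly people" as consequences of stroke. The Sample size calculation has one drop-out allowance of about 25%, not split between death and other loss.

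**The concern.** A patient who has died cannot be interviewed. Requiring valid clinical data therefore excludes that patient from the 12-month comparison, and what remains is selected by an event after randomisation. The phrase about receiving the complete programme deals with adherence only and does not bring these patients back.

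This differs from ordinary missing data. A functional score after death does not exist, so imputing one does not settle what is being compared.

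Deaths are foreseeable. Patients are 65 or older, enter directly after the acute hospital phase of a stroke and are followed for 12 months, and the Background describes coexisting multimorbidity as typical of this setting.

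If frailer patients die more often in one arm, that arm's survivors look better on average. An arm that keeps more frail patients alive looks worse. The Discussion intends implementation in the Dutch health care system if the programme proves effective and cost-effective, so readers should be able to see whether a functional difference holds once deaths count.

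**Working it through.** **1. The plan's own figure.** Inputs from the Sample size calculation: difference 3.5 FAI points, SD 8.9, power 0.8, alpha 0.05 (two-sided assumed). n = 2 × (1.960 + 0.842)² × 8.9² / 3.5² = 101.5, so 102 per group, as stated. The point does not depend on this figure; it supplies the SD and the scale.

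**2. What the rule does to a death.** Primary outcomes are interview scores. A death before 6 months leaves no score at either follow-up. A death between 6 and 12 months may still leave a 6-month score. The restriction to survivors therefore applies in full at 12 months.

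**3. Size of the shift, closed form.** Assumptions: normal latent FAI with SD 8.9, no true effect, and deaths taken from the low end of a frailty variable with correlation ρ to FAI. With death risk p, the survivor mean rises by 8.9 × ρ × φ(z_p)/(1 − p).

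- p = 10%: 0.1755/0.90 = 0.195
- p = 15%: 0.2332/0.85 = 0.274
- p = 20%: 0.2800/0.80 = 0.350

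Bias is the difference between arms (usual care first, then programme):

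- 10% v 15%: 8.9 × ρ × (0.274 − 0.195), which is 0.21 at ρ = 0.3 and 0.71 at ρ = 1
- 10% v 20%: 8.9 × ρ × (0.350 − 0.195), which is 0.41 at ρ = 0.3 and 1.38 at ρ = 1
- 10% v 10%: 0

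**4. Size with a logistic death model, with and without baseline.** Assumptions: FAI mean 20, SD 8.9, log-odds of death rising by 1 to 1.5 per SD of worse function, no true effect, deaths 10% usual care v 15% programme. The planned model is a regression and all four primary outcomes are measured at baseline. The article names no covariates, so adjustment for baseline FAI, with a baseline-to-12-month correlation of 0.6, is also assumed.

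| What drives death | Unadjusted shift | Baseline-adjusted shift |
|---|---|---|
| Latent 12-month score | +0.37 to +0.49 | +0.23 to +0.33 |
| Baseline frailty only | +0.20 to +0.29 | about 0 |

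If deaths in the first case are instead scored 0, the contrast is -0.65 to -0.73, against the programme. With the mortality rates exchanged (15% usual care, 10% programme), the unadjusted survivor contrast moves by the same amount against the programme, and a true 3.5 reads about 3.0 to 3.1.

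**5. Against the trial's precision.** With 102 per arm, SE = 8.9 × √(2/102) = 1.25. A shift of 0.5 is 0.5/1.25 = 0.4 SE and raises the two-sided false-positive rate from 5% to about 7%.

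**6. Costs.** The joint requirement for costs and clinical outcomes stands in a sentence about the effect data. The economic analysis has its own paragraph without that restriction. The wording can be read either way.

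**The case against.** The strongest objection is that the article states no rule for death. Handling of deaths, mortality tables and sensitivity analyses are commonly left to the full protocol or analysis plan. That stands for the missing detail: a reader might infer that deaths will go unrecorded or unreported, but absence from an outcome list in a condensed article does not show that. It does not remove the point, because the article fixes the analysis set and its label, and following that set as written gives a survivor comparison.

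A reader might also infer that costs incurred before death are certain to be discarded. The text does not establish this. The sentence concerns effect data, and care use is recorded continuously. Only the word for costs inside that sentence raises the doubt.

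Third, the bias is modest and conditional. Baseline adjustment reduces it, and it vanishes if baseline frailty alone drives death or if mortality and selection are equal. Larger shifts need one arm's mortality to be about double the other's, and the article gives no reason to expect that. It also excludes medically unstable patients and requires an expected return home. All of this stands and limits the size claimed.

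Fourth, measuring bias against a latent score for patients who died is itself a choice of estimand, and ranking death last is one legitimate option among several. That also stands, which is why the extra analysis is proposed only as a supplement.

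**Conclusion.** The point holds as a defect of definition and labelling: what is called intention-to-treat is, at 12 months, a comparison among survivors with data, and no listed outcome shows deaths beside it. With assumed deaths of 10% v 15% and no true effect, the FAI shift is about 0.4 to 0.5 points unadjusted and about 0.2 to 0.3 adjusted. Every scenario with no true effect stays below the 3.5-point target.

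The calculations do not support the inference that a survivor comparison would by itself produce a convincing false benefit. They do show that the sign of a small difference can depend on how deaths enter: about +0.4 to +0.5 among survivors against about -0.7 with deaths scored 0, on the same assumed data. All of this rests on assumed mortality, an assumed link between function and death, an assumed FAI mean and an assumed baseline correlation, since the document gives none of these. Loss of costs before death is a possible reading only.

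**What to change.** 1. In Data analysis, describe the 12-month functional comparison as one among survivors with data. Beside it, report deaths by 6 and 12 months by arm with a confidence interval. The interval will be wide: at 128 per arm, 15% v 10% is about 19 v 13 deaths, with half-width 1.96 × √(0.15 × 0.85/128 + 0.10 × 0.90/128) = 0.081, about 8 percentage points. It still shows the reader whether the arms differ visibly.
2. Add one supplementary analysis of FAI and Katz-15 over all randomised patients with known vital status, in which death ranks below the worst living score. Report it alongside the primary result, not as a condition for it.
3. State that the economic analysis keeps patients who died, with costs up to the date of death, and does not require a later clinical score.

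Cost: revised wording and a little more analysis. No new visit or instrument is needed, since vital status should become known when the 6- and 12-month interviews are arranged. The rank result will not be in FAI points.
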